#### Endpoints

*Primaryendpoint*: point estimate of sensitivity with 95% CI of the Cy-Tb test and Standard F TB assay.

*Secondaryendpoint*: point estimates of sensitivity and specificity with 95% CI of the Cy-Tb test and Standard F TB assay.

### Data analysis plan

Points estimates of sensitivity and specificity with 95% CI will be calculated based on Wilson score methods to accommodate for the loss of coverage in small samples. The Cy-Tb and Standard F TB test index accuracy will be evaluated to fit with the case definition and results compared with the QFT-Plus reference standard test results presented in table 1.

**Table 1 T1:** The case definition and results

	Definitions			
Test results		Tuberculosis infection	Not infected	Total
	Detected	True positive	False positive	True positive+false positive
	Not detected	False negative	True negative	False negative+true negative
	Total	True positive+false negative	False positive+true negative	Total

Concordant with the methods employed in a systematic review by WHO, we consider the rate of negative results to represent proxy specificity regardless of TB incidence and estimates.^20^ Differences in proportion of negative results between investigated tests and the reference test will be calculated. In addition, we will also calculate the rate of negative results on the Cy-Tb and Standard F TB tests among QFT-Plus negative participants.

Sensitivity is the percentage of participants with positive study tests among those with microbiologically confirmed TB (group 1).

Specificity is the percentage of participants with negative study tests among those at low risk for TB infection (group 3). We will also calculate the proportion of people with negative index tests among those at risk for TB infection (group 2).

The descriptive statistics will be calculated for the sample and the contingency table will be created to evaluate the diagnostic performance, including sensitivity, specificity and associated 95% CI for the Cy-Tb test and Standard F TB assay in comparison with the reference standard. The area under the curves, that is, areas under the receiver-operating characteristics curve will be calculated to estimate the comparative diagnostic accuracy of the Cy-Tb test and Standard F TB assay and QFT-Plus.

Multiple multivariate logistic regression models will be performed to adjust for confounders while analysing associations between participants characteristics and test accuracy. Subgroup analysis of test accuracy in different groups will be done with regard to gender, age, BMI, comorbidities, TB exposure, etc.

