### Study population

For objective 1, the study will enrol 100 eligible participants with microbiologically confirmed pulmonary TB at the National Lung Hospital, Hanoi, Vietnam for the purpose of verifying the sensitivity of (1) Cy-Tb and (2) Standard F TB for TB infection diagnosis. For objective 2, to evaluate the sensitivity and specificity of the Cy-Tb and Standard F TB tests for TB infection diagnosis, the study will recruit 250 eligible participants, including 200 household contacts of people with pulmonary TB and 50 people with known negative IGRA tests who report no history of exposure to TB.

*Group 1*: people with microbiologically confirmed pulmonary TB. The sensitivity of the Cy-Tb test and Standard F TB assay to diagnose TB infection will be confirmed in this group.

*Group 2*: household contacts of persons with bacteriologically confirmed, pulmonary TB. The sensitivity and specificity of the Cy-Tb test and Standard F TB assay to diagnose TB infection will be verified in this group.

*Group 3*: persons with known negative IGRA tests among those at low risk of TB infection. The specificity of Cy-Tb and Standard F TB for TB infection testing will be estimated using this group.

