###### Group 2 only

People without symptoms of active TB disease who are household contacts* of people with new microbiologically confirmed pulmonary TB who initiated treatment in Ha Noi, Vietnam.Have a normal CXR result.

**Household contacts: of a person with TB are defined as members who live under the same roof as the person with contagious pulmonary TB or who meet the following conditions*^4^:

*Sleeping under the same roof or sharing a kitchen space as TB-affected persons at least one night/week for3 monthsbefore the person was diagnosed with TB*.*Staying under the same roof with TB-affected persons for at least1 hour/day and continuously5 days/week for3 monthsbefore the person was diagnosed with TB*.

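### Group 2 intervals and sample size treat household contacts as independent, so the intervals may be too narrow if several contacts per household are enrolled

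*Protocol article*

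**What the plan says.** Under Study population, Objective 2 rests on 250 people, "including 200 household contacts of people with pulmonary TB"; the other 50 form Group 3. The Group 2 inclusion criteria define contacts as "members who live under the same roof as the person with contagious pulmonary TB", or people meeting shared-time conditions with that person. The protocol sets no maximum number of contacts per household or per index patient, and does not say how many households will supply the 200.

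Group 2 has two uses:
- **Accuracy against QFT-Plus.** Study population says: "The sensitivity and specificity of the Cy-Tb test and Standard F TB assay to diagnose TB infection will be verified in this group".
- **Raw negative rate.** The Data analysis plan adds the proportion of Group 2 that is negative on each index test.

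The interval method is stated once, in the Data analysis plan: point estimates of sensitivity and specificity carry 95% intervals "calculated based on Wilson score methods to accommodate for the loss of coverage in small samples". The same section plans logistic regressions of test accuracy on participant characteristics and subgroup analyses that include TB exposure. Clustering, a design effect or a robust variance is mentioned nowhere, including the Group 2 sample-size paragraph.

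**The concern.** Contacts of one index patient share the source, and much of the intensity, of their exposure. Infection status, and therefore test results, may be more alike within a household than between households. In that case 200 contacts carry less information than 200 unrelated people, and a binomial interval that ignores this covers the true value less often than stated.

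The Wilson method was chosen to protect coverage in small samples. It gives no protection against correlated observations. At stake is the stated precision of the Group 2 results, which supply 200 of the 250 participants for Objective 2. Point estimates stay the same.

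**Working it through.** **Inputs from the protocol (Sample size, Group 2):** 50% infected; sensitivity 75.8% for Cy-Tb and 88.9% for Standard F TB; half-width 0.1 at 95%; drop-out 10%; stated minimum 158 and 85; planned number 200.

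**Assumed inputs (not in the protocol):** m, the analysed contacts per household, 2 to 3; intraclass correlation (ICC) 0.1 to 0.3.

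**Step 1: reproduce the stated sample size.** Under independence, n = 1.96² p(1−p)/0.1², rounded up, then divided by 0.5 and by 0.9.
- Cy-Tb: 70.47, so 71; 71/0.5/0.9 = 157.8, so 158.
- Standard F TB: 37.91, so 38; 38/0.5/0.9 = 84.4, so 85.

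Both match with a design effect of 1, so the sample size contains no allowance for clustering.

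**Step 2: effect of clustering.** Design effect DE = 1 + (m−1) × ICC. The unadjusted interval is narrower than it should be by about 1 − 1/√DE. Its approximate coverage is 2Φ(1.96/√DE) − 1. The adjusted interval is the Wilson interval at n/DE. For Cy-Tb sensitivity, n = 200 × 0.9 × 0.5 = 90 QFT-Plus-positive contacts and p = 0.758. For the raw negative rate, n = 200 × 0.9 = 180, with p = 0.5 for illustration.

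| m | ICC | DE | Too narrow by | Coverage of nominal 95% | Half-width, Cy-Tb sensitivity | Half-width, negative rate | Cy-Tb minimum (158 × DE) |
|---|---|---|---|---|---|---|---|
| 1 | any | 1.00 | 0% | 95.0% | 0.087 | 0.072 | 158 |
| 2 | 0.1 | 1.10 | 5% | 93.8% | 0.091 | 0.076 | 174 |
| 3 | 0.1 | 1.20 | 9% | 92.6% | 0.095 | 0.079 | 190 |
| 2 | 0.3 | 1.30 | 12% | 91.4% | 0.099 | 0.082 | 206 |
| 3 | 0.3 | 1.60 | 21% | 87.9% | 0.110 | 0.091 | 253 |

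**Step 3: margin in the planned 200.** By the protocol's own formula, 200 tolerates a design effect up to 200/158 = 1.27 for Cy-Tb and 200/85 = 2.35 for Standard F TB. Standard F TB therefore keeps the 0.1 target over the whole assumed range (85 × 1.6 = 136). Cy-Tb misses it at the upper end. At DE 1.30 the two calculations straddle the target: the planning formula asks for 206, while the Wilson half-width is still 0.099.

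**Step 4: which Group 2 quantity is most exposed.** The raw negative rate uses every contact and largely reflects infection status, so household clustering of infection acts on it directly. Sensitivity and specificity condition on QFT-Plus status, and only part of each household enters each denominator. With 3 contacts per household and 50% infected, an analysed person's household contributes on average 1 + 2 × 0.5 = 2 same-status contacts if status is independent within households, and more if infection clusters. The relevant ICC there is that of index-test results given QFT-Plus status, which may be small.

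**The case against.** The best defence is that the problem is conditional. It needs more than one analysed contact per household and a positive correlation, and the protocol establishes neither. Eligibility is restricted to adults with no symptoms, a normal chest X-ray and no history of TB disease or infection, which limits how many members of one household can enter. With one contact per household, or no correlation, nothing changes. This stands, and it is why the finding is that intervals may be too narrow.

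A second defence concerns scope. The Data analysis plan defines sensitivity in Group 1 and specificity in Group 3, and names no interval method for the Group 2 negative rate. On those definitions the primary endpoint, sensitivity, is untouched. This also stands, but only in part. Study population places sensitivity and specificity in Group 2 as well, and the Wilson sentence makes no exception for it.

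A third defence is that a household identifier and a variance option are details for a case report form or an analysis plan that is not shown. That would answer a complaint about silence alone. Here, however, the protocol names an independence-based interval and states a sample size that reproduces without a design effect. The protocol does collect living situation and TB exposure, so it cannot be inferred that a link to the index patient will be absent.

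**Conclusion.** The concern holds in conditional form. The protocol recruits Group 2 through households without a one-per-household limit, and both its interval method and its sample size assume independence. Under the assumed 2 to 3 contacts per household and ICC of 0.1 to 0.3, the design effect is 1.1 to 1.6, intervals are about 5% to 21% too narrow, and coverage is about 94% to 88%. The raw negative rate is at greatest risk, provided a Wilson interval is used for it. The effect on accuracy conditional on QFT-Plus status is probably smaller.

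A reader might infer more than the protocol supports:
- **That Group 2 intervals are certain to be too narrow.** Neither the contacts per household nor the ICC is given.
- **That the difference in negatives between index and reference tests is a main casualty.** Every participant has all the tests, so that difference is paired within person and shared infection status largely cancels. No interval method is stated for it.
- **That regression p-values are bound to be too small.** The modelled outcome is test accuracy, not infection, and no standard-error method is fixed.
- **That Group 2 is too small.** The planned 200 absorbs a design effect of about 1.27 for Cy-Tb and 2.35 for Standard F TB.
- **That Groups 1 and 3 share the problem.** They are not recruited by household.

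**What to change.** Record an index-household identifier for each Group 2 participant at enrolment; linking contacts to households later may be difficult. For Group 2, replace the plain Wilson interval with a household-clustered one: either Wilson with n divided by the design effect estimated for that denominator, or a bootstrap that resamples households. State which interval applies to the raw negative rate. Use cluster-robust standard errors in any regression that includes Group 2. Keep plain Wilson for Groups 1 and 3. If only one contact per household is in fact enrolled, saying so would settle the point.

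The cost is one field in the electronic case report form and cluster options in Stata, which is already the planned software. The downside is slightly wider Group 2 intervals; if clustering proves negligible they will barely change.

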#### Statistical software

The data analysis will be performed using Stata V.17 or higher and Microsoft Excel V.2016 or higher for initial visualisation of the data.

### Significance

A simple, affordable and accurate test for TB infection can potentially make real changes in high-burden TB countries. The tests included in the study (Cy-Tb and Standard F) both have positive and negative attributes, and it is important to evaluate their performance in a high TB burden country such as Vietnam. If more people are correctly diagnosed with TB infection, preventative treatment can be provided and active cases can be averted, which in turn will decrease the number of people transmitting TB. The success of TB programmes is highly dependent on the active diagnosis and treatment of TB infections, which is not often performed in many high-endemic countries due to limited resources. The study will provide objective evidence for countries with high TB burden to issue new guidelines on the diagnosis of TB infection. However, a limitation is that the reference standard used in the study (QFT-Plus assay) also has suboptimal sensitivity, but is currently the best available test for the diagnosis of TB infection and is recommended by the WHO.

### Patient and public involvement

At this stage of the study, the tests under evaluation have not been implemented programmatically. Consequently, community participation in research will be limited. The project involves 350 individuals with TB infection or IGRA negative from the community. By involving participants in the study conducted in their community, the study aims to raise awareness about TB and the implications of early TB infection diagnosis within this community. Community members will be invited to any results dissemination meetings that are organised.

## Ethics and dissemination

### Ethics considerations

#### Regulatory and ethics approvals

The study will comply with the regulations on research ethics according to the Declaration of Helsinki and CIOMS guidelines as well as Vietnam’s national laws and regulations.

The study was granted ethical approvals from the Vietnam National Lung Hospital Institutional Review Board (65/23/CN-HDDD-BVPTU) and the Swedish Ethical Review Authority (Dnr 2023-04271-01).

#### Informed consent process

Research participants will be briefed on the content and significance and provided with ICFs, which must be signed to participate in the study. Any risks or benefits of participating in the study will be described in detail in the consent form.

#### Data management and protection

##### Data management

Research staff will record clinical data and laboratory results directly onto electronic case report forms (eCRFs) designed by Freundeskreis Für Internationale Tuberkulosehilfe e.V (FIT) in the ONA^21^ system. In cases where direct recording using the eCRFs is not possible, all data will be imported from paper CRF into ONA by site staff.

##### Missing data

Queries will be sent to study sites to correct erroneous data or complete missing information. We will not impute missing data.

##### Confidentiality and privacy

Participant information sheets will be stored in a locked cabinet and will be made accessible only to research staff. Data files, additional inputs and other profile information will be confidential. All participant information will be securely stored and encrypted and only pseudonymised data will be analysed, to ensure confidentiality and protect individual privacy.

### Safety considerations

Since this study will not use the test results to guide patient care, and considering the minimal risk associated with additional study procedures such as Cy-Tb and blood sample collection, the likelihood of a study participant experiencing serious adverse events (SAE) related to the investigational products is very low.

All AE-related information will be recorded. The SAE will be reported to FIT and all relevant authorities.

### Study benefits, costs or payments

#### Study benefits

There is no known direct benefit to participants for being in this study. The anticipated future benefit is improved diagnostics of TB infection. All participants who test positive on the QFT-Plus test will receive TB preventive treatment in accordance with the guidelines established by the Vietnam National Tuberculosis Programme.^7^

#### Cost or payments

Participants will receive the amount of 200 000 VND per study visit as reimbursement for study-related costs. There is no cost to participants or their healthcare provider if they participate in this study.

### Dissemination plan

Results will be published in an international journal and results only be presented at an aggregate group level without the risk of identifying individual study participants.
